### Component 5: Health economic evaluation calculating the relative cost effectiveness of inpatient rehabilitation services provided by the NHS and the independent sector 

Component 5 (C5) will address research question 5:

5.Is inpatient rehabilitation more cost effective when provided by the independent sector or the NHS, after adjusting for differences between the sectors in terms of key predictors of costs such as patient characteristics and length of stay?

The main cost-utility analysis (CUA) will use information from C1 and C3 to calculate the incremental cost per quality-adjusted life-year (QALY) gained by using independent sector rehabilitation services compared to NHS rehabilitation services, over the 18-month period. The largest costs are expected to be due to inpatient rehabilitation days (i.e. the primary statistical outcome), but the cost perspective will also include other NHS and Personal Social Services resource use to describe the wider support provided to participants.

The supporting cost-effectiveness analysis will calculate the incremental cost per readmission avoided (this is the secondary statistical outcome) for those discharged during the 12-month recruitment period in C1/C3. We will also conduct a supportive analysis including all patients discharged during the 18-month follow-up period of C1/C3.

Quality-adjusted life-years (QALYs) will be calculated from patients’ utility scores captured in C1 and C3 over the 18-month period, calculated in turn from EQ-5D-5 L (a 5-item generic health-related quality-of-life questionnaire plus visual analogue scale) responses using standard methods and a secondary analysis will calculate these from ReQOL (the 10-item Recovering Quality of Life questionnaire designed for users of mental health services) responses. These two quality-of-life questionnaires will be completed with patient participants at recruitment (C1) and through telephone or videoconferencing at 6, 12 and 18 months follow-up (C3). We will use the resource use data gathered via the key staff contact about patient participants discharged from the inpatient rehabilitation unit they were receiving treatment in at recruitment, as well as the inpatient costs pre-discharge, to calculate costs and quality-adjusted life-years per patient. These resources include the length of the baseline inpatient rehabilitation admission from the study baseline date (i.e. the date the patient participant was interviewed for C1), any readmissions in days, the use of supported accommodation services (including the length of time the participant has lived there, the level of support provided [residential care, 24 h supported housing, < 24 h supported housing] and the weekly costs) and any individual ‘care packages’ provided, including the number of hours of support per week, the cost per week and the length of time provided. Unit costs for inpatient bed-days will be calculated using a bottom-up microcosting in the first instance so that the independent and NHS services are assessed according to the cost to the provider of providing the services.

C5 will also include cost efficiency analyses using information on inpatient rehabilitation bed-days from C1, C3, and C4, calculating the mean and marginal costs per patient across the two types of service provision, to further investigate the impact of service type around the primary statistical outcome of total inpatient days.

#### Analysis

The primary analysis perspective will be that of the NHS plus Personal Social Services, so rehabilitation costs for users of NHS services will be captured as number of inpatient days, monetised using unit costs that we will calculate from a bed-day micro-costing across the two arms. Secondary analyses will use (i) published NHS unit costs also for the inpatient rehabilitation costs in both arms, and (ii) the cost charged to the relevant CCG for users of independent sector rehabilitation services. Other health and social care resource use provided after discharge will be costed according to NHS Reference Costs and Personal Social Service Research Unit (PSSRU) unit costs [40] for all analyses. QALYs will be calculated from utility scores using standard area-under-the-curve methods and adjusted for baseline values.

The bed-day micro-costing will use certain items from the QuIRC (avoiding duplication of questions), supplemented by other information from the key staff contact or team in order to provide a mean unit cost per patient for the two settings, including: staffing levels and salaries (mean cost per hour, also consider holiday pay, sick leave, etc.); staff to patient ratios; number of patients per ward; number of patients on ward with similar diagnosis; estates costs and other overheads (including ward floor square metres); medication costs; ‘hotel’ facilities (food, laundry etc.); travel or other similar costs (e.g. to visit local area, to access community resources). The questions will be developed with the independent providers and staff at NHS sites to ensure they are appropriate and will yield meaningful information.

Bootstrapping will be used to calculate means and 95% confidence intervals for costs and QALYs to show the probability that rehabilitation in the independent sector is cost-effective compared to in the NHS for a range of cost-effectiveness threshold values. We will report a cost-effectiveness plane (CEP) and cost-effectiveness acceptability curve (CEAC) using the bootstrapped results.

We will conduct secondary cost-efficiency analyses [41] using the patient-level bed-day data collected in C1, C3 and C4, calculating the cost per patient and marginal cost per patient incurred over the study time period, according to their assigned inpatient rehabilitation group (NHS or independent sector). These analyses will use the same unit costs and cost perspective as for the cost-per-QALY analysis (see above), although the NHS cost perspective will be narrower as the C4 cohort will not have direct information on resources used beyond those reported in the Mental Health Services Data Set (MHSDS).

Adjustment covariates will include relevant sociodemographic and clinical confounding variables captured in C1 (for the main cost-utility analyses) or provided with the MHSDS (for the cost-efficiency bed-day analyses). Predictors of any missingness will be assessed and also included as adjustment covariates, and sensitivity analysis will assess the impact of uncertainty in assumptions and input parameters.

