#### Patient eligibility criteria

All patients of inpatient rehabilitation units that are participating in the study will be eligible for participation, with the exception of those on leave (with or without formal permission) at the time of recruitment (this comprised 8% of patients in the REAL study [4]) and those who lack adequate English to give informed consent (1% in the REAL study [4]). The vast majority of patients at these units have a diagnosis of schizophrenia or bipolar affective disorder (89% in the REAL study [4]).

We will include patients in C1 who are assessed as lacking capacity. We expect only a minority of eligible patients to lack capacity (around 8% based on the REAL study [4]) but it is important they are included in the study in order to prevent sample bias [4].

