#### Procedures for patient recruitment and data collection

Managers of inpatient services selected for potential participation will be contacted by the research team via telephone and/or email to explain the purpose of the study, why their service has been selected, and what would be required of the manager, the staff, and the patients if they agree to participate in the study.

Once a service has agreed to participate, the research team and service manager will arrange a time for the researcher to visit the inpatient service to recruit participants and collect data. It is expected that the researchers will spend approximately one week in each service. The researcher will interview the service manager to collect service level data. The researcher will also meet with the rehabilitation unit staff to explain the purpose and processes of the study. Staff will be asked to approach eligible patients and asked if they would like to meet the researcher to discuss the study.

Informed consent will be collected from patients who have capacity and agree to participate. The patient research interview will then be conducted and once completed, the patient will be offered £20 for their participation [30].

All efforts will be made to maximise the capacity of each patient to be able to provide informed consent for the study (for example, by explaining the purpose and process of the study in simple terms and over multiple meetings), and any patient with capacity who declines participation will not be included. However, for eligible patients who lack capacity to give informed consent we will seek advice from a consultee on their participation. Research data for participants lacking capacity will be collected via staff interview and healthcare records, but these participants will not be asked to participate in an interview themselves.

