For all participants recruited to C1, we will also attempt to complete the 10-item version of the Recovering Quality of Life measure (ReQOL) and the EQ-5D-5 L at six, 12 and 18 months after recruitment. We will explain to patient participants during the consent procedure for C1 that we will ask them to take part in brief follow-up interviews six, 12 and 18 months later by telephone or video call (Teams or Zoom). We will ask participants for their contact number at baseline (i.e. data collection for C1) and attempt to contact them directly at follow-up. If we are unable to make contact this way, we will contact them through their healthcare team i.e. the member of staff researchers are contacting monthly; for inpatients this will be the ward manager and for those who have been discharged, their community care co-ordinator.

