In this two-stage approach, an initial regression generates a propensity score, the probability of ‘exposure’ (admission to an independent sector unit) conditional on sociodemographic and clinical covariables identified in C1. The propensity score is then included in a second appropriate regression, accounting for clustering, in which the main outcome variable is successful rehabilitation at 18 months (defined as before). This approach allows us to account for the principal confounders influencing why (e.g. the patient’s health state) a person is admitted to an independent sector unit rather than an NHS unit (i.e. confounding by indication). A major issue when estimating propensity scores is the presence of missing values in the explanatory variables. Multiple imputation will be used to handle missing data under missing at random (MAR) assumption, and the two-stage analysis will be performed in each imputed dataset. The results are then combined using Rubin’s rule to obtain an overall estimate of the effect of service sector on successful rehabilitation. We will also conduct sensitivity analyses following the methods recommended by Blake et al. [37] if the MAR assumption is not considered plausible.

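### Component 5: adding predictors of missingness as covariates cannot recover incomplete QALYs or costs, and the rule is not limited to baseline variables

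*Protocol article*

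**What the plan says.** All of this is in the protocol article.

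- **Covariates (Component 5, Analysis).** For the main cost-utility analysis: "Adjustment covariates will include relevant sociodemographic and clinical confounding variables captured in C1". The next sentence adds the missing-data rule, "Predictors of any missingness will be assessed and also included as adjustment covariates", and ends with a general promise that "sensitivity analysis will assess the impact of uncertainty in assumptions and input parameters". No imputation, weighting or likelihood method is named for missing utilities or costs.
- **QALYs (Component 5, Analysis).** "QALYs will be calculated from utility scores using standard area-under-the-curve methods and adjusted for baseline values".
- **Timing (Component 3, Procedure and data collection).** Besides the recruitment interview, the team will try to obtain ReQOL and "the EQ-5D-5 L at six, 12 and 18 months after recruitment".
- **Participants lacking capacity (Component 1).** They are included and expected to be "around 8% based on the REAL study" of eligible patients. At recruitment, "these participants will not be asked to participate in an interview themselves"; their data come from staff and records.
- **Other components.** Component 3 names multiple imputation for explanatory variables, and its propensity-score analysis says "Multiple imputation will be used to handle missing data under missing at random (MAR) assumption". Component 4 allows multiple imputation where suitable.

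**The concern.** Two separate problems follow from the sentence.

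First, a covariate on the right-hand side of a model does nothing for a patient whose outcome is missing. An area-under-the-curve QALY needs all four utilities, so one missed interview removes the patient's QALY and wastes the interviews that were done. Missing cost items raise the same difficulty. Participants lacking capacity have no self-reported baseline utility, although the article includes them in Component 1 precisely to avoid a biased sample.

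Second, the confounders are tied to variables collected at recruitment, but the predictors of missingness are not. Discharge is a plausible predictor. The fallback route for follow-up contact differs between inpatients and discharged patients, and resource use after discharge depends on the key staff contact. Discharge also lies between sector and outcome: it ends the baseline inpatient days, and the article expects inpatient days to be the largest cost. Adjusting for it in the outcome model would condition on part of the effect that Component 5 sets out to estimate.

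**Working it through.** **The plan's own sample size.** Component 3 supplies the patients for the cost-utility analysis. A two-sample t test for 0.38 SD with 90% power and a two-sided 5% level needs 146.5, so 147 per group, or 294. The variance inflation factor is 1/(1 − 0.16) = 1.19, and 294 × 1.19 = 350. The design effect is 1 + (8 − 1) × 0.06 = 1.42, and 350 × 1.42 = 497. These figures reproduce and are not in dispute. They concern inpatient days, not QALYs.

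**Patients who can have a complete QALY.** Inputs: 500 recruited (Component 1, Sample size) and 8% lacking capacity (Component 1, Patient eligibility criteria). Applying the 8% to the recruited sample, and taking every interviewed patient to have a baseline utility, are assumptions. Then 500 × (1 − 0.08) = 460.

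**Follow-up losses.** The article gives no rate, so let m be the assumed proportion missing at each of 6, 12 and 18 months. If waves are missed independently, the complete count is 460 × (1 − m)³. If the same patients miss every wave, it is 460 × (1 − m).

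| m | Independent | % of 500 | Same patients | % of 500 |
|---|---|---|---|---|
| 10% | 460 × 0.729 = 335 | 67 | 460 × 0.9 = 414 | 83 |
| 20% | 460 × 0.512 = 236 | 47 | 460 × 0.8 = 368 | 74 |
| 30% | 460 × 0.343 = 158 | 32 | 460 × 0.7 = 322 | 64 |

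**Discharge by sector.** Component 3, Sample size estimation, expects 160/250 = 64% of NHS and 80/250 = 32% of independent sector patients to be discharged during the 12-month recruitment period.

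**Illustration of adjusting for discharge.** This is a simulation of 400,000 patients with assumed effects. Discharge probabilities are 64% and 32%, discharge adds 0.06 QALY, and sector acts only through discharge. The true sector effect is therefore 0.06 × (0.32 − 0.64) = −0.0192 QALY. Between 14% and 32% of QALYs are missing, and simulation error is about 0.0006.

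| Missingness depends on | Complete cases, baseline covariate only | Complete cases, discharge added | Imputed using discharge, baseline covariate only in outcome model |
|---|---|---|---|
| Baseline covariate (two runs) | −0.0185, −0.0201 | 0.0009, −0.0008 | −0.0185, −0.0201 |
| Discharge (two runs, opposite directions) | −0.0179, −0.0198 | 0.0007, −0.0006 | −0.0187, −0.0198 |

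The imputation was a single regression imputation of the whole QALY, which is enough to check the point estimate but not the standard error. In this set-up, dropping incomplete records did little to the estimate. Putting discharge in the outcome model removed the effect almost entirely, because all of it was assumed to pass through discharge.

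**The case against.** The strongest reply is that the sentence describes a covariate set and excludes nothing. The article never calls the analysis complete-case, it condenses a longer protocol, and a health economic analysis plan could add imputation. That stands: a reader might infer that Component 5 is fixed as a complete-case analysis, and the text does not say so. But the sentence is a stated rule, not an omission. Even with imputation added elsewhere, it would still send predictors of missingness into the outcome model.

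A reader might also infer that Component 5 contradicts Component 3. It does not. In both Component 3 analyses the imputation is introduced for missing explanatory variables, so nothing there commits the team to imputing repeated outcomes.

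A third tempting reading is that the sector effect will be adjusted away. No sentence names discharge as a predictor of missingness, and since the other covariates come from Component 1, a baseline-only reading is natural. With baseline predictors that explain the missingness, the illustration shows no bias beyond simulation error. The harm is therefore conditional. The text does not rule it out, though, and research question 5 lists length of stay among the adjustment factors without saying whether stay before or after recruitment is meant.

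Finally, the counts rest on assumed rates, and participants without capacity at recruitment cannot be said to lack every later utility, since follow-up is to be attempted for everyone recruited. What they lack is the baseline value, and without it the QALY over the full 18 months is incomplete.

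**Conclusion.** The concern holds in a limited form. The one missing-data step stated for Component 5 cannot recover incomplete QALYs or costs and leaves observed utilities unused. Under the stated assumptions, complete QALYs would number 158 to 335 of 500 if waves are missed independently and 322 to 414 if the same patients miss every wave, at 30% down to 10% missing per wave.

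Whether this costs only precision or also causes bias depends on the predictors chosen. Baseline predictors that explain the missingness cost mainly precision. A post-baseline predictor on the path from sector to cost and QALY could remove part of the sector effect. The rule as worded permits that choice but does not make it.

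**What to change.** Replace the sentence with a named method:

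- Use multiple imputation of wave-level utilities and costs, run separately by sector and combined with the bootstrap that Component 5 already plans.
- Use post-baseline predictors of missingness, such as discharge status, in the imputation model only.
- Limit the outcome-model covariates to baseline variables.
- Report as sensitivity analyses a complete-case analysis and one excluding participants lacking capacity. For the latter group, imputed utilities would lean heavily on staff-rated and record data, and the comparison shows how much that matters.

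This extends to outcomes an approach that Component 3 describes only for explanatory variables. It needs revised wording and some extra computing, but no new data. The price is reliance on a missing-at-random assumption for utilities and costs.

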## Discussion

This is the first large scale, empirical study to compare NHS and independent sector services in any medical specialty and our approach and results may therefore be useful for other areas of health care, especially those that currently use independent sector provision alongside the NHS. Whilst we have considerable experience of conducting research in the field of mental health rehabilitation successfully in the NHS, this is our first attempt to collaborate with the independent sector on research of this scale. The assessment of clinical and cost effectiveness poses specific challenges, given the potential sensitivity of the results. We are therefore encouraged at the positive reception the project has received from our NHS and independent sector partners who are keen to collaborate and learn from the study results which we hope will inform how these different sectors can work together to optimise efficiency and clinical outcomes for patients.

## Data Availability

No datasets were generated or analysed during the current study.

## Abbreviations

ACER: Assessing the Clinical and cost-Effectiveness of inpatient mental health Rehabilitation services provided by the NHS and independent sector
EQ-5D-5L: EuroQol 5-Dimension 5-Level health related quality of life questionnaire
C1: Component 1
C2: Component 2
C3: Component 3
C4: Component 4
C5: Component 5
CANSAS: Camberwell Assessment of Needs Short Appraisal Scale
CAT: Client Assessment of Treatment
CCG: Clinical Commissioning Group
CEAC: Cost-Effectiveness Acceptability Curve
CEP: Cost-Effectiveness Plane
CQC: Care Quality Commission
DAGs: Directed Acyclic Graphs
DE: Design Effect
HoNOS: Health of the Nation Outcome Scale
HRA: Health Research Authority
IVA: Instrumental Variable Analysis
LSP: Life Skills Profile
MANSA: Manchester Short Assessment of Quality of Life
MAR: Missing At Random
NHS: National Health Service
NICE: National Institute for Health and Care Excellence
NIHR: National Institute for Health and Care Research
OAT: Out-of-Area-Treatment
PMG: Project Management Group
PPI: Patient and Public Involvement
QuIRC: Quality Indicator for Rehabilitative Care
REAL: Rehabilitation Effectiveness for Activities for Life
ReQOL: Recovering Quality of Life questionnaire
SD: Standard Deviation
UCL: University College London
UK: United Kingdom
VIF: Variance Inflation Factor
